#### Effectiveness

2.7.3

The effectiveness of Strolll AR for improving TUG, FTSTS, 10MWT, Mini-BESTest, and FES-I will be analyzed according to the per-protocol principle for participants who have completed the final assessment, randomized into control and intervention groups using the 20 concealed randomizations. For each outcome parameter, independent-samples *t*-tests (or their non-parametric equivalents) will be used to compare Control (i.e., using the change scores during the control period; T0-T1) and Intervention groups (i.e., using the change scores during the intervention period; T1-T2). We expect significantly higher change scores for the Intervention group than for the Control group. The 20 predefined concealed randomizations will enable us to perform multiple between-group comparisons, yielding a sensitivity analysis to test the robustness of the effectiveness findings in this pragmatic RCT. That is, this innovative analysis approach will not only provide us with a one-shot indication of the statistical effect, but also with a confidence interval of this effect. Furthermore, multiple randomized comparisons will reduce the likelihood of a systematic confounding effect biasing this pragmatic RCT results, as is often the case when a single one-shot randomization would result in Control and Intervention groups differing significantly at baseline in certain demographic or clinical characteristics. With a multiple-shots randomization, potential effects associated with significant between-group differences in demographics or clinical characteristics of a single randomization will average out over the multiple shots.

As a secondary analysis, which is possible given the design in which all per-protocol participants performed the same T0-control-T1-intervention-T2 procedure, a complementary within-subjects comparison will be performed using repeated-measures ANOVAs with the within-subject factor Time (three levels: T0, T1, T2) for the TUG, FTSTST, 10MWT, Mini-BESTest and FES-I, comparable to the analysis performed in Hardeman et al. (15). For significant main effects of Time, the first and second reverse Helmert contrasts will be used to evaluate Control and Intervention effects, respectively. This will help us interpret (a potential null-finding of) the pragmatic RCT as such a within-subjects comparison is less susceptible to between-subjects variation than a between-groups comparison.

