**Figure 2 fig2:**
[figure not shown]
Schematic of the study design.

The definition of a pragmatic RCT is that the intervention is tested in a real-world population in a real-world setting (i.e., the clinic), with an appropriate comparison arm (i.e., usual care alone in the current study) and relevant outcomes to determine its effectiveness (24, 25). Special trial designs can be considered. In this particular pragmatic RCT, all participants follow the same T0-control-T1-intervention-T2 procedure, suitable for both between-groups and within-subjects comparisons of the Strolll AR intervention effects as well as for evaluating its clinical feasibility. With regard to the between-groups comparison, participants will be allocated to control (using T0-T1 change data) or intervention (using T1-T2 change data) groups using multiple (*n* = 20) two-armed randomizations following a 1:1 ratio (Figure 3). The randomization will be predefined by an independent person using a Matlab (26) script (see Supplementary material S5), locked with a date and timestamp, and kept concealed from participants, therapists, and researchers. After the final T2 assessment of the last participant, the 20 randomizations of participants over control and intervention groups will be revealed to the researchers and applied in the data analysis (as detailed in section 2.7.3). Participants, therapists, and researchers will therefore all be blind to group allocation during the study, which is impossible for rehabilitation interventions with traditional RCT or cross-over designs. Note that a longitudinal design with a fixed order for all participants may be prone to time-dependent confounding factors, such as progressive worsening of Parkinson’s disease symptoms over time. We would like to emphasize that potential time effects associated with disease progression work conservatively against finding intervention effects. This particular pragmatic RCT design is not recommendable for situations where conditions improve over time (e.g., natural recovery after acute stroke), as this would promote arbitrary intervention effects associated with natural improvement in conditions over time. This design, in which all participants receive the Strolll AR intervention, further allows for a complementary within-subjects evaluation of the intervention effect (i.e., being less susceptible to between-subjects variation than aforementioned between-groups evaluation), while at the same time providing ample information on the clinical feasibility of the Strolll AR platform implemented in the clinical pathway in terms of its safety, adherence, performance, and user experience (i.e., from both participants’ and therapists’ perspectives), making efficient use of scarcely available resources (e.g., funding limiting scientific staff, time limiting availability of clinical staff, patients limiting the number of participants). Moreover, a design with the same procedure for all participants makes implementation of this study in the clinical pathway easier (hence the term pragmatic RCT) and potentially reduces the dropout rate because no participants are withheld from receiving the intervention due to the randomization.

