### Sample size calculation

2.4

A convenience sample of 100 participants will be included and measured from approximately 10 clinics in a time frame of 9 months. This sample size will give the therapists of the clinics enough experience with the Strolll AR platform and intervention to evaluate feasibility from a therapists’ perspective (e.g., usability, acceptability, safety). For our effectiveness outcomes, an a-priori required sample-size calculation in G*Power 3.1.9.7 showed that 58 participants (i.e., 29 per group) is sufficient for identifying statistically significant between-group differences (usual care vs. Strolll AR intervention). This is based on 80% power and a two-tailed alpha error of 5% and a minimal improvement of 2.57 s in TUG [i.e., the average of the smallest detectable TUG difference of Lim et al. (40) and Huang et al. (41)] and an effect size of 0.755 [Cohen’s *d* statistic; SD of 3.4 s; (41)]. Accounting for approximately 10 dropouts during the usual-care period, approximately 10 exclusions during the pre-intervention in-clinic phase (i.e., participants deemed unable to take the glasses home after one-to-three in-clinic training sessions) and approximately 10 dropouts during the intervention period at home [estimates based on Hardeman et al. (15)], recruiting a total of 100 participants should be sufficient for obtaining the minimal groups sizes required for identifying between-group differences. As dropout rates are taken into account, participants who are not completing the study will not be replaced. Plans to reduce dropouts are a voucher as a token of appreciation for their participation, updates about study progression via a newsletter send to participants and therapists every 2 months to keep them involved in the study and having weekly online or onsite check-ins with the participating therapists.

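### The spread of effect estimates over 20 re-splits of the same completers is not a confidence interval of the effect, and no single primary estimate is named

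*Protocol article*

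**What the plan says.** The protocol article's section 2.1 (Study design) has every participant follow the same sequence of baseline, usual care, T1, intervention and T2. An independent person prepares 20 "two-armed randomizations following a 1:1 ratio", which are locked and concealed. After the last T2, "the 20 randomizations of participants over control and intervention groups will be revealed to the researchers and applied in the data analysis".

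Section 2.7.3 (Effectiveness) then compares, in each randomisation, the T0-T1 changes of those labelled control with the T1-T2 changes of those labelled intervention, by independent-samples t-test or a non-parametric equivalent. The analysis set is the participants who completed the final assessment. The article calls the 20 comparisons a sensitivity analysis for robustness and adds that the approach will "not only provide us with a one-shot indication of the statistical effect, but also with a confidence interval of this effect". It gives no formula for that interval and does not say which of the 20 results is the primary one. The repeated-measures analysis on all completers is secondary, although the article itself notes that "such a within-subjects comparison is less susceptible to between-subjects variation than a between-groups comparison".

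Section 2.4 sizes the trial for one two-group comparison on TUG: "58 participants (i.e., 29 per group) is sufficient for identifying statistically significant between-group differences".

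**The concern.** A confidence interval has to reflect how much the estimate would vary if a new sample of patients were drawn. Re-splitting one fixed sample 20 times shows how much the estimate varies with the labels. The two quantities need not be close. If the spread over splits is published as the interval of the effect, readers will take it as the precision of the main effectiveness result.

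There is a second consequence. Twenty t-tests on the same people will often not agree, and the article does not name the estimate on which the conclusion rests. A mixed result, with some splits significant and others not, would have no defined meaning.

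**Working it through.** **The plan's own figure.** Inputs from section 2.4: "80% power and a two-tailed alpha error of 5"%, "a minimal improvement of 2.57 s in TUG", SD 3.4 s, "an effect size of 0.755" (2.57/3.4 = 0.756). A two-sided two-sample t-test with d = 0.755 needs 28.53, so 29 per group and 58 in total, with power 80.7%. The figure reproduces, for one comparison of two groups.

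**Algebra of one split.** For completer i, let C be the T0-T1 change and I the T1-T2 change. Let z = +1 if labelled intervention and -1 if control, with n completers split equally. Then

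D = (2/n)·Σ(z=+1) I − (2/n)·Σ(z=−1) C = mean(I − C) + (1/n)·Σ z(I + C).

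The first term does not involve z, so it is the same number in all 20 splits, and so is its sampling error. Only the second term varies between splits. This needs no assumption about the data.

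**Size.** Assumptions: n = 100 − 10 − 10 − 10 = 70 completers (the losses expected in section 2.4); both changes have SD σ; their correlation is ρ; normal data. The article does not give ρ. T1 enters the two changes with opposite sign, so negative values are plausible: ρ = −0.5 if the changes are only independent occasion noise of equal variance. For seconds, σ = 3.4 is used; the coverages do not depend on it.

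- SD between splits: a = σ·√(2(1+ρ)/n)
- Standard error of mean(I − C): b = σ·√(2(1−ρ)/n)
- Standard error of the 20-split average: c = √(b² + a²/20)
- Approximate coverage of mean ± 1.96 SD: 2Φ(1.96·a/c) − 1

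| ρ | a (s) | b (s) | c (s) | 1.96·a/c | Approx. coverage | Simulated coverage |
|---|---|---|---|---|---|---|
| −0.8 | 0.257 | 0.771 | 0.773 | 0.65 | 49% | 48% |
| −0.5 | 0.406 | 0.704 | 0.710 | 1.12 | 74% | 71% |
| 0 | 0.575 | 0.575 | 0.589 | 1.91 | 94% | 93% |
| +0.5 | 0.704 | 0.406 | 0.436 | 3.17 | 99.8% | 99.5% |

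Simulated values are a little lower because the SD is itself estimated from 20 results. Other constructions give other figures: the 2.5 to 97.5 percentiles of the 20 estimates cover 41%, 65%, 87% and 98% at the same four values of ρ, and mean ± t·SD/√20 covers 12%, 21%, 35% and 54%.

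**What 20 tests would conclude.** Simulated share of trials declared positive when there is no effect:

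| Rule | ρ = −0.5 | ρ = 0 | ρ = +0.5 |
|---|---|---|---|
| One pre-named split | about 5% | about 5% | about 5% |
| Any of 20 | about 26% | about 42% | about 57% |
| More than half | about 2% | below 1% | below 1% |

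The figure for 20 independent tests, 1 − 0.95²⁰ = 64%, does not apply because these tests are dependent. At the planned 2.57 s effect, the 20 tests disagree (1 to 19 significant) in 38% of trials at ρ = −0.5 and 55% at ρ = 0.

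**The alternative.** A paired interval for mean(I − C) covers 94.6% to 95.3% at every ρ tried. Its mean width is 2.80 s at ρ = −0.5 and 2.28 s at ρ = 0, against about 3.23 s for one split. At d = 0.755 and ρ = −0.5 its power is 95%, against 88% for one split of 35 and 35. Its variance, 2(1−ρ)σ²/n, is below the 4σ²/n of one split for every ρ > −1.

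**The case against.** The best defence is that the article calls the 20 comparisons a sensitivity analysis, gives no interval formula, and may leave the combination of results to a separate analysis plan. Part of this stands. That the interval is the spread over the 20 results is an inference, though the natural one, and a separate plan could supply a combination rule. It could not make the published sentence true of that spread. Nor is a single primary comparison named for the sensitivity analysis to be sensitive to.

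The secondary repeated-measures analysis does not fill the gap. Its contrasts are used only after a significant Time effect, and the second reverse Helmert contrast sets T2 against the mean of T0 and T1, which is not the difference between the two changes.

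Some stronger readings are tempting but not supported:

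- **That the splits are chosen after the data are seen.** They are predefined, locked and concealed; only their application is late.
- **That the interval is always too narrow.** It is too narrow for negative ρ, close to nominal at 0 by coincidence, and too wide for positive ρ.
- **That the spread holds no between-person variation.** The split noise is driven by it. What is missing is the sampling error of mean(I − C).
- **That the false-positive rate is inflated.** Nothing says that one significant split means success. Each single test holds 5%, and a majority rule is conservative.
- **That the 80% power is misstated.** Section 2.4 claims it for one comparison only.

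**Conclusion.** The concern holds in this form: section 2.7.3 describes split-to-split variation as a confidence interval of the effect, which it is not, and names no single primary estimate. The first part follows from algebra once the interval is read as the spread over the 20 results. The size rests on assumptions (70 completers, equal SDs, normal data, unknown ρ). For mean ± 1.96 SD, coverage runs from about 48% at ρ = −0.8 to over 99% at ρ = +0.5, with under-coverage on the more plausible, negative side. The error rate of the overall conclusion is undefined rather than shown to be inflated: it ranges from about 2% or less under a majority rule to between 26% and 57% under an any-of-20 rule, for ρ from −0.5 to +0.5. This affects the main effectiveness result and should be settled before the randomisations are revealed.

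**What to change.** Make the primary effectiveness result one estimate on TUG: the within-person difference between the T1-T2 change and the T0-T1 change in all analysable completers, with its own 95% confidence interval and one test (a one-sample t-test or the equivalent mixed-model contrast). Report the 20 splits only as a description of split-to-split variation, with no confidence-interval label and no count of significant results.

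If a between-group result must stay primary, name one of the locked randomisations in advance and report its ordinary t interval. That is valid but less precise, because each split uses only one of the two changes per person.

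No new data are needed. The cost is that the 20 randomisations no longer count as inferential evidence, and that the matching text in the abstract, section 2.1 and section 2.4 must be aligned with section 2.7.3. The change corrects the precision only. It does not remove period effects from the fixed order or selection from the per-protocol analysis set.

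### In the secondary within-subjects analysis, the contrast labelled as the Intervention effect includes half of the usual-care change and is not the intervention-period change

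*Protocol article*

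**What the plan says.** Section 2.7.3 (Effectiveness) of the protocol article plans a primary between-group comparison and a secondary within-subjects one.

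- **Primary:** the control group contributes its change "using the change scores during the control period; T0-T1", and the intervention group its change "using the change scores during the intervention period; T1-T2".
- **Secondary:** all per-protocol participants enter "repeated-measures ANOVAs with the within-subject factor Time (three levels: T0, T1, T2"), one for each of the five effectiveness outcomes. Contrasts follow only "For significant main effects of Time", and then "the first and second reverse Helmert contrasts will be used to evaluate Control and Intervention effects, respectively".
- **Purpose of the secondary analysis:** "This will help us interpret (a potential null-finding of) the pragmatic RCT".

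Section 2.1 (Study design) accepts that the fixed order "may be prone to time-dependent confounding factors, such as progressive worsening of Parkinson’s disease symptoms over time". The plan therefore does not assume that nothing changes between T0 and T1.

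**The concern.** Reverse Helmert contrasts compare each level with the mean of all earlier levels. On three occasions the first is T1 against T0, which fits the Control label. The second is T2 against the average of T0 and T1. That average straddles the usual-care period, so the result is not the change from the start to the end of the intervention period, although it is labelled the Intervention effect.

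Its role raises the stakes. If participants improve equally in both periods, for example through repeated testing or continuing physiotherapy, a null between-group result is correct. The analysis meant to explain that null could then report an Intervention effect that owes part of its size to usual care. If participants worsen under usual care, the same contrast understates the change during Strolll AR.

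**Working it through.** **Inputs from the documents (section 2.4, Sample size calculation).** TUG difference 2.57 s, SD 3.4 s, d = 0.755, two-sided alpha 5%, power 80%, recruitment of 100 with three losses of about 10, so 100 − 30 = 70 completers.

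**The plan's own figure.** 2.57/3.4 = 0.756. A two-sample t-test at d = 0.755 needs 28.53, so 29 per group and 58 in total. The stated 58 reproduces, and nothing below alters it.

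**Algebra.** With weights on (T0, T1, T2):

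- first reverse Helmert contrast: (−1, 1, 0) = T1−T0
- second reverse Helmert contrast: (−½, −½, 1) = (0, −1, 1) + ½(−1, 1, 0) = (T2−T1) + 0.5(T1−T0)
- period difference: (1, −2, 1) = (T2−T1) − (T1−T0)

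The second contrast equals T2−T1 only when the mean T0-to-T1 change is zero.

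**Worked TUG values** (seconds; a negative change is an improvement):

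| T1−T0 | T2−T1 | Second Helmert | Period difference |
|---|---|---|---|
| 0 | −2.57 | −2.57 | −2.57 |
| −2.57 | 0 | −1.285 | +2.57 |
| −1 | −1 | −1.5 | 0 |
| +1 | −1 | −0.5 | −2.0 |

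**How often it would mislead.** Assumptions: 70 completers and independent errors between occasions. The documents give no occasion SD, so three are shown:

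- 0.93 s = 2.57/(1.96 × √2), if 2.57 s is read as a pure measurement-error limit
- 1.5 s, an intermediate value
- 2.40 s = 3.4/√2, if 3.4 s is read as the SD of a change

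The 0.5 s gains are also assumed. The standard error of the second contrast is √1.5 × SD/√70, which is 0.136, 0.220 and 0.351 s.

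- Equal 0.5 s gains: the contrast estimates 0.5 + 0.25 = 0.75 s, or 5.5, 3.4 and 2.1 standard errors.
- A 0.5 s gain in usual care only: it estimates 0.25 s, or 1.8, 1.1 and 0.7 standard errors.

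Simulated share of trials in which both the Time test and the second contrast are significant:

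| True TUG gain | SD 0.93 s | SD 1.5 s | SD 2.40 s |
|---|---|---|---|
| 0.5 s in each period | about 100% | 91% | 49% |
| 0.5 s in usual care only | 44% | 18% | 8% |

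In the second row T2−T1, tested on its own, stays at 5%. In the first row the period difference stays at about 5%, as it should when Strolll AR adds nothing to usual care.

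**The case against.** **The weights are not written out.** Under forward Helmert coding the second contrast would be T1 against T2. The first would then be T0 against the mean of T1 and T2, which cannot be a Control effect. Only the reverse reading fits the labels.

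**T0 and T1 can serve as a double baseline.** If usual care produces no change, averaging them gives a more precise estimate (√1.5 against √2 times the occasion SD). This is a fair reason to choose the contrast, but the plan does not make the interpretation conditional on a zero usual-care change, and section 2.1 anticipates change over time.

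**The Control contrast is reported alongside.** This helps in part. With a 0.5 s gain in usual care only and SD 0.93 s, the Control contrast is also significant in 39 of the 44 percentage points. With 0.25 s gains in both periods it is so in only 27 of 73.

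**The expected direction is conservative.** If disease progression dominates, the contrast shrinks the effect. False credit needs improvement under usual care, which is possible but not shown. This limits the worry about overstatement; the estimate is still not the intervention-period change.

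**The Time test acts as a gate.** With no true change at all, it holds the second contrast to about 2 to 3%. It gives no protection here, because usual-care change alone can open it. Keeping or dropping the gate is otherwise largely a matter of preference.

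**A stronger reading is tempting:** that the plan never compares the two periods. The documents do not support it. The primary analysis sets T0-to-T1 change against T1-to-T2 change between randomized halves, and section 2.7.2 compares weekly falls between the periods with a paired test. The gap is confined to the secondary within-subjects analysis of the effectiveness outcomes.

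**Conclusion.** The point holds for the secondary analysis and should be fixed. The identity is exact: half of the usual-care change, with its sign, enters what is labelled the Intervention effect, for all five outcomes. How often this would mislead is uncertain. For a 0.5 s usual-care gain with no later gain, the rate runs from about 8% to 44% across the assumed SDs; for equal 0.5 s gains, from about 49% to 100%. These rates depend on the assumed gains, on independent occasion errors and on 70 completers. The bias itself does not.

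A reader might infer that this undermines the trial's main conclusion. The documents do not support that: the analysis is declared secondary and complementary, nothing lets it override the between-group comparison, and the primary test and the sample size of 58 stand.

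**What to change.** In section 2.7.3, replace the reverse Helmert contrasts with repeated contrasts: T1−T0 for the control period and T2−T1 for the intervention period, each with a confidence interval. Add (T2−T1) − (T1−T0), pre-specified, as the within-subject comparison of Strolll AR with usual care. T2−T1 alone restores the section's own definition of the intervention-period change, but it cannot show benefit beyond usual care.

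The change takes one or two sentences. The cost is precision. At occasion SD 2.40 s and 70 completers the standard errors are:

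- second Helmert contrast: √1.5 × 2.40/√70 = 0.35 s
- T2−T1: √2 × 2.40/√70 = 0.41 s
- period difference: √6 × 2.40/√70 = 0.70 s, twice the Helmert value

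Power of the period difference at 2.57 s is still about 95%. For a 1 s gain confined to the intervention period, power before any gate is about 80%, 68% and 29% respectively.

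The period difference also counts T1 twice, so a one-off practice gain between T0 and T1 biases it against Strolll AR. With a 0.5 s gain followed by none, at SD 0.93 s, it is significant in that direction in about 44% of trials. It should therefore be read beside the two single-period changes, not alone.

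### The within-subject contrast offered to help read a null result is an uncontrolled estimate of a different quantity, and the precision reason given for it misleads

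*Protocol article*

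**What the plan says.** Section 2.7.3 (Effectiveness) makes the main comparison an independent-samples test on change scores: T1-T2 change in one half of the completers against T0-T1 change in the other half, over 20 concealed splits. A secondary repeated-measures ANOVA over T0, T1 and T2 follows for all five effectiveness outcomes. If Time is significant, the first reverse Helmert contrast is read as the control effect and the second as the intervention effect. The stated purpose is: "This will help us interpret (a potential null-finding of) the pragmatic RCT as such a within-subjects comparison is less susceptible to between-subjects variation". Section 2.1 (Study design) gives the same reason, describing the within-subject evaluation as "being less susceptible to between-subjects variation than aforementioned between-groups evaluation".

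**The concern.** The reason suggests that both analyses measure the same effect and that the secondary one does so with less noise. Two things count against this. First, a change score already removes each person's stable level, so the main source of between-person noise is absent from the primary. Second, the second Helmert contrast does not subtract the change seen under usual care. If people improve a little in both periods, for instance through practice on tests taken three times, the primary is correctly null while the Helmert contrast can still be significant. A reader following section 2.7.3 could then conclude that the effect exists and the between-group test was merely too noisy to show it.

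**Working it through.** **Inputs from the protocol.** Section 2.4: "a minimal improvement of 2.57 s in TUG", "an effect size of 0.755", SD 3.4 s, two-sided 5%, 80% power, "58 participants (i.e., 29 per group) is sufficient". Of 100 recruited, three losses of about 10 leave about 70 completers. Section 2.1: "two-armed randomizations following a 1:1 ratio", so 35 per half.

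**Assumptions.** 3.4 s is the SD of a change (section 2.4 does not say whether it refers to a change or a single score). Visit errors are independent. The drift sizes below are assumed; the protocol gives none. One split is simulated at a time.

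**The plan's own figure.** 2.57/3.4 = 0.756. With d = 0.755 the noncentral t gives 79.2% power at 28 per group and 80.7% at 29, so 58 reproduces. At 35 per group power is 87.6%.

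**What each analysis estimates.** Let D1 = T0 − T1 and D2 = T1 − T2 (positive means a faster TUG).
- Primary: mean D2 in one half minus mean D1 in the other.
- Paired version: mean of (D2 − D1) in everyone. Averaged over all possible 1:1 splits, the primary estimate equals this.
- Second reverse Helmert: (T0 + T1)/2 − T2 = D2 + 0.5·D1.

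With no treatment effect and a gain g in each period, the expected values are 0, 0 and 1.5g.

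**Standard errors.** Error variance per visit is e² = 3.4²/2 = 5.78; n = 70.

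| Estimate | Variance | SE |
|---|---|---|
| Primary | 8e²/n = 46.24/70 = 0.661 | 0.81 s |
| Paired D2 − D1 | 6e²/n = 34.68/70 = 0.495 | 0.70 s |
| D2 alone | 2e²/n = 11.56/70 = 0.165 | 0.41 s |
| Second Helmert | 1.5e²/n = 8.67/70 = 0.124 | 0.35 s |

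The 2.31-fold fall in SE is 1.15 (pairing) × 1.73 (not subtracting the control change) × 1.15 (averaging T0 and T1). In simulation, between-person SDs of 0, 3.4 and 7 s left the primary SE at 0.81 to 0.82 s, so stable differences do not blur it.

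**If people differ in how they change.** Hold the change SD at 3.4 s and let ρ be the correlation between D1 and D2. The paired variance is 2 × 11.56(1 − ρ)/70 and the Helmert variance is 11.56(1.25 + ρ)/70. Independent visit errors give ρ = −0.5, hence 0.70 and 0.35 s. At ρ = 0 they are 0.57 and 0.45 s; pairing then gives 0.81/0.57 = 1.41-fold and the switch of contrast 0.57/0.45 = 1.27-fold. How the precision gain divides therefore depends on ρ. The formula D2 + 0.5·D1 does not.

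**Simulation with no treatment effect** (20,000 trials per scenario for the improvement and no-drift rows; Helmert counted only after a significant Time effect; the primary rejects in about 5% throughout).

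| Equal change per period | Null primary with favourable Helmert |
|---|---|
| none | about 1% |
| 0.3 s improvement | 15% |
| 0.5 s improvement | 46% |
| 0.8 s improvement | 86% |
| 0.3 or 0.5 s worsening | 0 of 8,000 trials each |

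At 0.5 s the figure runs from 19% (change SD 5 s) to 91% (change SD 2 s). With a person-specific slope SD of 2 s, the three improvement rows become 11%, 27% and 59%. The paired test stays at about 5% under equal gains.

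**Same pattern under a real effect.** With a true effect of 1 s and no drift, the primary rejects in 23%, the paired test in 29% and the Helmert contrast in 70%. A null primary with a favourable Helmert occurs in 50%, close to the 46% seen with a shared gain of 0.5 s and no effect. The pattern alone cannot tell the two apart.

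**The case against.** A reader might infer that the within-subject result is held back to explain away a null primary, or gives effectiveness a second route to success. The protocol does not support that. The analysis is pre-specified, labelled secondary, planned for every effectiveness outcome and run whatever the primary shows. The null finding appears only in brackets, and no rule lets the secondary establish effectiveness.

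Nor is the precision reason simply false. Variation in individual change is also between-subjects variation, and it adds more to the split comparison than to the Helmert contrast (slope variance enters as 4/N against 2.25/N). Pairing also has real value: 1.15-fold in SE is worth a third more participants (1.15² ≈ 1.33), and the gain is larger at higher ρ. This supports pairing, however, and not the contrast that was chosen. Under persistent individual slopes the paired D2 − D1 is the estimate whose SE does not move (0.70 s), while the Helmert SE rises from 0.35 to about 0.50 s.

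The percentages need improvement over time, whereas section 2.1 expects worsening, under which the problem vanishes. That stands. But section 2.1 argues conservatism only for disease progression, concedes that a fixed order is open to time confounding, and does not discuss practice on repeated tests.

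Finally, the first Helmert contrast examines the control period and can warn the reader. It does so only in part. In a separate run it was also significant in 3 of 16 percentage points at 0.3 s, 12 of 45 at 0.5 s and 44 of about 86 at 0.8 s. A significant intervention contrast beside a non-significant control contrast is not a comparison of the two periods.

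**Conclusion.** The point holds as a flaw in the choice and justification of the secondary contrast. By algebra, and under no assumption about variances, the second Helmert contrast adds half the usual-care change where the primary subtracts all of it. It is an uncontrolled pre-post estimate and cannot show that a null controlled comparison was merely imprecise. The stated reason is misleading as applied, because stable between-person differences already cancel in the primary.

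Under independent visit errors, most of the Helmert contrast's smaller SE comes from not subtracting the control change and from averaging two pre-measures. With more variation in individual change, pairing accounts for a larger share. The 15%, 46% and 86% depend on the assumed equal gains and on reading 3.4 s as an SD of change. It would be wrong to infer a test with an inflated error rate in general: without drift the pattern appears in about 1% of trials.

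**What to change.** In section 2.7.3, use the paired contrast (T1-T2) − (T0-T1), with its 95% CI, for the within-subject reading of effectiveness. For TUG, set that interval against the planned 2.57 s. At 70 completers its half-width is about 1.995 × 0.70 = 1.4 s under the assumptions above, so an estimate near zero would exclude 2.57 s and a null result could be read directly. Power at 2.57 s is about 95%, against 87 to 88% for a single split.

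Report the second Helmert contrast as descriptive, and state that it does not support effectiveness when the primary is null. In sections 2.1 and 2.7.3, replace the between-subjects reason with the accurate one: pairing removes person-specific variation in change that the split comparison leaves in.

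The paired contrast protects against gains that are equal in both periods. Unequal time effects remain in it, as they do in the primary.

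Cost: wording in two sections and one paired estimate for each of the five outcomes, with no new data. The reported SE will look less favourable than that of the Helmert contrast.
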